**Randomization:**

Mothers will be randomized at the time of enrollment by blinded envelope to either one of the treatment group or a placebo group in a 1:1 ratio.

**Outcome measures:**

1. **Placenta**

a) Morphometry – weight and size of the placenta.

b) Micrography - number of terminal villi, vasculature and collagen content.

c) Immuno- histochemistry – proliferation, apoptosis and differentiation.

d) Enzyme immunoassays - Heat shock protein 90, Lipid hydroperoxide, Nitrotyrosine assay Paraoxonase 1 expression and Superoxide dismutases

e) RNA and protein analyses of placental tissues - RNA for gene microarray analyses

1. **Pregnancy Outcomes**
   1. Complications of pregnancy – extent of pre-eclampsia, preterm labor
   2. Gestation at delivery
   3. Need for resuscitation at delivery
   4. Cord gas characteristics at delivery
2. **Brain injury and development at term by MR Imaging (see table 2) based on:**
   1. Qualitative MRI injury- white matter injury (WMI) and gray matter injury (GMI)
   2. Brain Metrics on MR imaging
   3. Diffusion- apparent diffusion coefficient (ADC) and fractional anisotropy (FA)
   4. Spectroscopy- lactate and NAA levels in the basal ganglia
   5. Advanced MRI development indices – brain volumes, surface based morphology (SBM, folding indices)
3. **Neurobehavior at term equivalent and neurodevelopmental outcome at 18-24 months** MDI and PDI by Bayley Scale of Infant Development (BSID III) (> 2SD from the norm, score ≤ 70)

***Table 1.*** Summary of the study and procedures for infants recruited into the study

| **Age** |  | **Pregnancy** | **Birth** | **38-41 weeks CGA** | **Discharge** | **18-24 months** |
| --- | --- | --- | --- | --- | --- | --- |
| Maternal data |  | X | X |  |  |  |
| Clinical data |  |  | X | X | X | X |
| Ellagic acid |  |  | X |  |  |  |
| MRI imaging |  |  |  | X |  |  |
| Neurodevelopmental  Behavioral measures | Neurologic/  Sensory |  |  | Dubowitz | Hearing |  |
|  | Attention |  |  | HNNE  attention |  |  |
|  | Global cognition |  |  |  |  | BSID-III  Cognitive |
|  | Motor |  |  |  |  | BSID-III  Motor, Neuro |
|  | Language |  |  |  |  | BSID-III  Language |

* HNNE- Hammersmith Neonatal Neurological Examination Optimality Score

* MRS- MR Spectroscopy; SBM- Surface-based morphology

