Fetuses with impaired intrauterine growth often suffer from long term placental insufficiency and subsequent chronic hypoxia not dissimilar from infants suffering from acute perinatal injury with subsequent hypoxic ischemic injury. Many IUGR infants tend to not tolerate labor secondary to their inability to withstand the transient drops in placental blood flow that accompanies normal labor. As a group these infants are twice as likely to have low apgar scores, twenty times more likely to suffer from encephalopathy, five times more likely to suffer perinatal stroke, and ten times more likely to die in the neonatal period [16-18]. Furthermore, these fetuses have a 2 to 3 fold increased risk of delivering prematurely placing them at additional risk of long term morbidity and mortality [19]. MR imaging in premature infants suffering from IUGR show decreased intracranial volume, abnormal diffusion of the posterior limb of the internal capsule, decreased cerebral gray matter, and reduced hippocampal volume that persists through term when compared to gestational aged matched controls [20, 21]. Magnetic resonance spectroscopy in these infants displays elevated lactate and creatine in the white matter, further indicating hypoxemic and nutritional injury. In long term neurodevelopmental follow up patients born with IUGR have an increased risk of developing cerebral palsy and continue to have deficits in learning, cognition, and attention up through adolescence [22-28]. These findings are more pronounced when focusing on the more severe end of the IUGR spectrum, those with evidence of abnormal umbilical flow (absent or reversed end diastolic flow) or birth weight < 3rd percentile [29-31]. This central nervous system injury is likely mulifactorial, with mechanisms such as altered placental flow, repeated hypoxemia, elevated cortisol levels from alterations of the hypothalamic-pituitary-adrenal (HPA) axis regulation, nutritional deprivation, and acidosis after birth all contributing [18, 32]. Given that the majority of infants with IUGR are diagnosed prenatally by standardized ultrasound measurements (usually end of the 2nd trimester) this population represents an ideal model for testing the impact of a prenatal neuroprotectant.

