**Inclusion criteria:**

- Expecting mother with a fetal diagnosis of intrauterine growth restriction (IUGR) defined by estimated birth weight ≤ 10th percentile for gestational age and gender based on the Alexander growth curves.
- ≥ 6 weeks from expected due date.

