**Exclusion Criteria:**

- Multiple congenital abnormalities (other than CHD)
- Known fetal chromosomal disorder
- Maternal illicit drug or alcohol intake

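### Gestation at delivery is to be tested without adjustment for gestation at enrolment, which costs precision but does not bias; pre-eclampsia and preterm labor also lack a time origin

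*Protocol*

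**What the plan says.** The inclusion criteria require a fetal diagnosis of growth restriction and enrolment "≥ 6 weeks from expected due date". With a due date at 40 weeks, entry closes at about 34 weeks. No lower limit is given, and the background (A potential model) places the usual diagnosis near the end of the second trimester. The only maternal item among the exclusions is "Maternal illicit drug or alcohol intake", so existing pre-eclampsia does not bar entry. Under Randomization, "Mothers will be randomized at the time of enrollment by blinded envelope".

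Under Outcome measures, the pregnancy outcomes include, as complications, "extent of pre-eclampsia, preterm labor", and separately "Gestation at delivery". Neither carries a time origin.

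Biostatistical Analyses assigns continuous variables to a t-test or Mann-Whitney test and categorical variables to chi-squared or Kruskal-Wallis. No baseline term appears. The same section names brain injury and delayed development as the primary outcomes and calls the trial a pilot for a larger one.

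**The concern.** A woman enrolled at 33 weeks cannot deliver before 33 weeks; a woman enrolled at 25 weeks can. Part of the spread in gestation at delivery is therefore already settled at randomisation, and the planned test treats it as noise. With 40 women per arm, a chance difference in entry gestation can also pass into the result.

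Pre-eclampsia raises a separate question. If disease present before the first glass of juice is counted as an event, both arms carry cases that the juice could not have prevented. That pulls a yes/no contrast towards no effect, and hides harm as much as benefit. Because the pilot is meant to inform a larger trial, an event rate that mixes existing and new cases would carry over into that trial's planning.

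**Working it through.** The Protocol states no power, effect size, SD or pre-eclampsia rate, so there is no figure of its own to reproduce. From the Protocol: 80 women, 1:1, so 40 per arm; entry up to about 34 weeks; unadjusted tests. Everything else below is assumed.

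**1. Is the raw gestation comparison biased?** Mean gestation at delivery = mean gestation at entry + mean interval. Randomisation balances the first term in expectation, so the expected raw difference equals the expected difference in interval. In simulations with a true gain of 1 week, the mean estimate was 1.0 week by raw test, interval and regression in every scenario.

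**2. Chance imbalance at entry.** For uniform entry over a range of width w, SD = w/√12, and the SD of the difference between arm means is SD × √(2/40).
- 24-34 weeks: 10/√12 = 2.89; 2.89 × 0.2236 = 0.65 week.
- 28-34 weeks: 6/√12 = 1.73; 1.73 × 0.2236 = 0.39 week.

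The part that reaches the raw result is this figure times the slope β of delivery gestation on entry gestation.

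**3. Precision.** Simulation: 40 per arm, entry uniform over 24-34 weeks, true gain 1 week, two-sided 5%.
- A: delivery gestation nearly unrelated to entry (mean 36, SD 3, kept above entry).
- B: interval unrelated to entry (mean 5, SD 2.5 weeks).
- C: interval averages 0.6 of the time left to 37 weeks, SD 2.

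| Scenario | SD raw | SD interval | Power raw | Power interval | Power regression |
|---|---|---|---|---|---|
| A | 2.85 | 3.98 | 34% | 19% | 35% |
| B | 3.76 | 2.42 | 21% | 45% | 43% |
| C | 2.26 | 2.55 | 49% | 40% | 63% |

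The pattern follows from Var(interval) − Var(raw) = Var(entry) × (1 − 2β). The interval fixes the slope at 1, so it beats the raw outcome only if β exceeds 0.5. With Var(entry) = 8.33, the SDs above imply β of about 0.04 (A), 1.00 (B) and 0.42 (C). Regression estimates β, so it does about as well as the better alternative, or better still.

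**4. Pre-eclampsia counted yes/no.** With share q affected at entry and new-onset risk p, the counted risk is q + (1 − q)p. The difference between arms is (1 − q) times the new-onset difference. Take assumed new-onset risks of 30% v 15%.

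| q | Counted risks | Risk ratio | Power, all cases (40 per arm) | Power, new onset in unaffected women |
|---|---|---|---|---|
| 0 | 30.0% v 15.0% | 0.50 | 36% | 36% |
| 5% | 33.5% v 19.3% | 0.57 | 30% | 34% |
| 10% | 37.0% v 23.5% | 0.64 | 26% | 33% |
| 20% | 44.0% v 32.0% | 0.73 | 20% | 30% |
| 30% | 51.0% v 40.5% | 0.79 | 15% | 27% |

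At q = 10%, 0.10 + 0.90 × 0.30 = 0.370 and 0.10 + 0.90 × 0.15 = 0.235; the difference falls from 15 to 13.5 points. Among unaffected women the ratio stays at 0.50.

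Harm is masked in the same way. A true doubling from 10% to 20% appears at q = 10% as 28% v 19%, a ratio of 1.47.

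**The case against.** An unadjusted t-test in a randomised trial is valid, and covariate adjustment is an efficiency choice that a statistical analysis plan, not shown here, may contain. The same plan may hold an onset rule for pre-eclampsia. These outcomes are not primary, and the pilot has low power for them with or without the changes.

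Most of this stands, and it limits the point to a low-severity improvement. What remains is that the Protocol does state the test for continuous outcomes and that test has no baseline term. A later onset rule also works only if status at enrolment was recorded. Table 1 collects maternal data in pregnancy and Biostatistical Analyses mentions maternal risk factors, so the item may be captured, but pre-eclampsia at entry is not named.

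A reader might infer two stronger claims.
- *That raw gestation at delivery dilutes a true effect because entry gestation bounds it from below.* It does not: randomisation makes the expected difference the same as for the interval, and only precision and chance imbalance are at issue.
- *That pre-eclampsia present at entry is counted as an outcome.* The Protocol does not say so; it is silent. Moreover, *extent* may mean graded severity. Worsening of existing disease happens after randomisation and could respond to treatment, so dilution would be smaller than the yes/no figures show.

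**Conclusion.** The point holds as one of precision, with a smaller one of definition.

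**Gestation at delivery:** the planned comparison is unbiased but can be inefficient. The gain from adjustment ranged from almost nothing (34% to 35% power) to substantial (21% to 43%), depending on how strongly delivery gestation follows entry gestation, which the Protocol does not let one estimate. The 0.65-week chance imbalance rests on the assumed 24-34 week spread; a 28-34 week spread gives 0.39.

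**Pre-eclampsia and preterm labor:** the lack of a time origin leaves room for disease present at randomisation to count. For pre-eclampsia, a yes/no count would shrink the risk difference by exactly the share affected. That share and the new-onset risks are assumptions; the direction is not.

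Neither primary outcome is touched. Severity is low, and the case for acting is that the change is cheap.

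**What to change.** 1. Analyse gestation at delivery by linear regression on arm plus gestation at enrolment. The eligibility check already needs that value, so no new data are required. Do not substitute the interval from randomisation to delivery: it had less power than the raw outcome in two of the three scenarios.
2. Record pre-eclampsia and preterm-labor status at enrolment as named baseline items.
3. Define each complication as new onset after randomisation among women without it at enrolment. Report worsening separately in women who already had it, and say whether *extent* is a grade or a yes/no count.

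The cost is two baseline entries and a few sentences. The one downside is a smaller new-onset denominator: 36 per arm instead of 40 if 10% are affected at entry, and 32 if 20% are.

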**Biostatistical Analyses**

**General methods:**

The statistical methods employed in this study will be complex and will be undertaken with the assistance of [name], biostatistician in the Department of Pediatrics. Clinical data such as maternal risk factors, birth weight, placental weight, gestation, need for resuscitation in the DR, etc. will be collected for both the intervention and the control group during the perinatal course.

The primary outcomes will be either a) brain injury or b) delayed development at 18-24 months. The relationship of placental function and measures to these outcomes will be explored to understand the mechanism of neuroprotection.

Brain injury will be defined as any of the following (see Table 3):

- Moderate to severe injury by qualitative scoring of WMI or GMI
- Diffusion scores (ADC, FA) > 2 SD from normal term infants
- Spectroscopy showing elevated lactate and decreased NAA (hypoxic injury) over the L basal ganglia
- Bottom 25% percentile in brain metrics, volumetric indices, or measures of surface based morphology (SBM) compared to the general healthy population.

Delayed development will be classified as:

- BSID III (MDI or PDI) > 2 SD (< 70) below the normal population

* MRS- MR Spectroscopy; SBM- Surface-based morphology

Table 2. Definition of CNS Injury by US/ MRI

| **Modality** | **Technique** | **Measures** | **Likelihood of injury** | **Definition of**  **Injury** |
| --- | --- | --- | --- | --- |
| Ultrasound |  | Grade IVH | Low | Grade 2-4 |
| MRI | Qualitative | WMI, GMI | Low | Mod-Severe injury |
|  | Diffusion/Spect | ADC, FA  Lactate, NAA | High  Low | > 2 SD above term  Lactate ↑, ↓NAA |
|  | Metrics | Intraparietal diameter, extra cranial space | High | Bottom 25% of the population |
|  | Volumetric | Total volume,  Cerebral gray matter volume, | High | Bottom 25% of the population |
|  | SBM | Cortical surface area, average sucal depth, integrated folding index | High | Bottom 25% of the population |

Continuous variables will be compared using a student t-test when they are parametric and Mann-Whitney test when they are nonparametric. Categorical variables (such as moderate or severe white matter injury) will be compared using either a chi-squared (for parametric) or a Kruskal-Wallis test for nonparametric one way analysis of variance. This is a pilot study where the results will assist in the planning of a larger randomized controlled trial.

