**Interpretation of results:** We expect pomegranate-exposed placentas to show less evidence of oxidative stress, more trophoblast mass, and less evidence of fibrin deposition microscopically and by immunoblotting. We expect less apoptosis and more evidence of trophoblast differentiation in the pomegranate group. We will consider any differences in the light of biological significance, also, as small statistically significant differences may prove relevant to the infant outcomes. Although highly unlikely based on the known effects of pomegranate, we will note any adverse effect from pomegranate extract, such as enhanced oxidative stress, increased fibrin deposition as a sign of injury, or diminished terminal villi lower than control.

Infant Neurobehavior: All infants will have a formal Dubowitz neurologic exam and an attention evaluation using the Hammersmith Neonatal Neurological Examination Optimality score at term equivalent (38-41 weeks post menstrual age). Furthermore, formal neurodevelopmental follow up will take place at 18-24 months of age.

MRI Evaluation

If clinically stable, MRI will be undertaken without sedation at term equivalent (38-41 weeks CGA). The MRI evaluation will include the following analysis:

a) Systematic qualitative scoring of the nature and extent of brain injury

b) Diffusion analysis of the cortical, white matter and posterior limb of the internal capsule to generate apparent diffusion coefficients (ADC).

c) Spectroscopy over the left basal ganglia

d) Brain metrics measuring the length of certain regions of the brain and comparing to standardized values

e) Assessment of MRI developmental indices such as volume and surface folding (SBM)

| **Measure** | **White Matter** | **Gray Matter** |
| --- | --- | --- |
| Qualitative | WM lesion score/  ventriculomegaly | Cortical and DNGM injury score |
| Metrics | Frontal lobe volume, | Intrahemispheric volume loss, ventricular size |
| Volumetry | Total myelinated and unmyelinated WM volumes | Total cortical gray matter, DNGM and CSF volumes  Hippocampal volume |
| Diffusion | Two measures (ADC, RA) each measured on 8 pairs of volume –derived lesions | Two measures (ADC, RA) on:   1. 6 pairs of surface-based regions 2. 8 pairs of volume-derived regions |
| MRS | N/A | Lactate and NAA measures over the L basal ganglia |
| SBM | NA | Four measures (cortical surface area, average sulcal depth, integrating folding index, and percentage buried cortex) |

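### The diffusion criterion for brain injury names no region or summary although 88 regional values are planned, and its direction conflicts with the protocol's own reading of ADC and anisotropy

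*Protocol*

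**What the plan says.** The Protocol, under General methods in Biostatistical Analyses, states: "The primary outcomes will be either a) brain injury or b) delayed development at 18-24 months". It continues "Brain injury will be defined as any of the following" and lists four criteria. The diffusion criterion reads "Diffusion scores (ADC, FA) > 2 SD from normal term infants". Table 2 in the same section gives the diffusion cut-off as "> 2 SD above term" and rates the likelihood of diffusion injury as high.

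The measures table under MRI Evaluation shows what will be measured. For white matter it has "Two measures (ADC, RA) each measured on 8 pairs of volume –derived lesions". For gray matter the same two measures are taken on "6 pairs of surface-based regions" and "8 pairs of volume-derived regions". That table calls the second measure RA. The outcome list and the injury definition call it FA.

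The caption to Figure 4, on the pilot data, reports lower diffusivity in the anterior limb of the internal capsule, higher anisotropy in the left frontal lobe and lower diffusivity in the left centrum semiovale. It interprets these changes as more mature white matter in the pomegranate group.

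**The concern.** A 2 SD limit picks out the few percent of normal infants at the edge of a distribution, but only when it is applied to one value. Here the protocol fixes the limit and the case rule for a primary outcome without saying what the limit applies to. It could be one region, several, an average, or any of the 88 values.

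Under an any-value rule, much of what is called diffusion injury would be chance outliers in both arms, which dilutes a real difference. The flag would also depend on how many regions could be read. In the pilot only 30 infants were scanned from 41 randomised mothers, with movement one of the reasons, so incomplete regional data are plausible. If an any-value rule is not meant, the choice of region for a primary outcome stays open until data are seen.

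Direction is a second problem. The text counts both tails for both measures, and Table 2 counts high values of both. Either way, an infant with unusually high anisotropy is a case, although the pilot section treats higher anisotropy as favourable. The text also counts unusually low ADC as injury, which the pilot section again reads as favourable.

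**Working it through.** The protocol gives no expected rate for this criterion, so there is no figure of its own to reproduce.

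**Number of values** (MRI Evaluation, measures table)
- White matter: 2 measures × 8 pairs × 2 sides = 32.
- Gray matter: 2 × (6 + 8) pairs × 2 sides = 56.
- Total: 88, or 44 per measure, counting each side and taking RA to stand for FA.

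**One value, healthy infant, normal distribution**
- Two-sided: 2 × (1 − Φ(2)) = 0.0455, or 4.6%.
- One-sided: 1 − Φ(2) = 0.02275, or 2.3%.

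**At least one of 88, independent values**
- Two-sided: 1 − (1 − 0.0455)^88 = 0.983.
- One-sided: 1 − (1 − 0.02275)^88 = 0.868.

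**At least one of m, common correlation ρ** (two-sided form; the second Φ is dropped for one-sided)

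P = 1 − ∫ φ(u) [Φ((2 − √ρ·u)/√(1−ρ)) − Φ((−2 − √ρ·u)/√(1−ρ))]^m du

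The documents give no correlation, so ρ is an assumption and is varied. The two-block rows treat ADC and anisotropy as independent sets of 44, with P = 1 − (1 − P44)².

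| Healthy infants flagged (%) | ρ = 0 | 0.3 | 0.5 | 0.7 | 0.8 | 0.9 |
|---|---|---|---|---|---|---|
| 88 values, two-sided | 98.3 | 90.4 | 71.6 | 45.3 | 32.6 | 20.3 |
| 88 values, one-sided | 86.8 | 52.9 | 36.6 | 22.6 | 16.3 | 10.1 |
| Two blocks of 44, two-sided | 98.3 | 93.2 | 80.7 | 59.4 | 46.5 | 31.8 |
| Two blocks of 44, one-sided | 86.8 | 63.8 | 48.5 | 33.0 | 25.1 | 16.7 |
| ADC only (44), two-sided | 87.1 | 73.9 | 56.0 | 36.3 | 26.9 | 17.4 |
| ADC only (44), one-sided | 63.7 | 39.9 | 28.2 | 18.2 | 13.4 | 8.7 |

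With one ADC and one anisotropy summary, taken as independent, the rate would be 1 − (1 − 0.0455)² = 8.9% two-sided or 1 − (1 − 0.02275)² = 4.5% one-sided.

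**What a summary would gain.** Assumptions: 80 women split 1:1, so 40 scanned infants per arm at best; control ADC 0.5 SD above normal in all 44 regions; treated infants at normal; two-sided α 0.05. The mean z over 44 regions has variance ρ + (1 − ρ)/44 = 0.316, 0.511 and 0.707 at ρ = 0.3, 0.5 and 0.7, so its SD is 0.562, 0.715 and 0.841.

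- *Mean z compared as a continuous outcome:* 0.5/(SD × √(2/40)) = 3.98, 3.13 and 2.66. Power Φ(that − 1.96) = 98%, 88% and 76%.
- *Mean z cut at 2 of its own SDs:* controls flagged 1 − Φ(2 − 0.5/SD) = 13.3%, 9.7% and 8.0%, against 2.3% of treated. Power is about 45%, 28% and 21%.
- *Any ADC region, one-sided:* 68.9% against 39.9%, 52.5% against 28.2%, and 36.7% against 18.2%. Power is 75%, 60% and 46%.
- *Any ADC region, two-sided:* 80.6% against 73.9%, 63.5% against 56.0%, and 43.7% against 36.3%. Power is about 10% to 11% at each ρ.

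The binary rows use the two-proportion normal approximation with pooled variance under the null.

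**If the benefit is focal.** Suppose only 6 of 44 regions improve by 0.5 SD (an assumption). The mean moves by 6/44 × 0.5 = 0.068, and the continuous mean-z test has power of about 8.4%, 7.1% and 6.5%.

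**The case against.** The strongest reply is that the word any in the definition joins the four criteria and does not say that any region is enough. One score per measure fits the wording too. Choice of region and averaging are often left to an analysis plan, and none is shown here. This stands in part. A reader might infer that the plan, applied as written, labels half to nearly all healthy infants as injured. The documents do not support that. It needs the any-value reading, the two-sided wording and a correlation no higher than about 0.7 to 0.8. Table 2's wording gives lower rates.

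It does not remove the point. The protocol itself sets the threshold and case rule for a primary outcome, and the rule cannot be applied to the planned measurements without adding a step. The text and Table 2 disagree on sidedness, and neither direction agrees with the pilot section. Those are conflicts in what is stated, not details deferred.

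A second objection is that RA and FA are different names, so only the 44 ADC values match the criterion. Even then, one-sided at correlation 0.9, the rate is 8.7% against 2.3%.

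Third, averaging all regions is not clearly better. A binary cut on the mean has less power than a one-sided any-region flag, and the pilot effects were regional and partly one-sided in the brain, so a global mean could dilute them. This is correct and shapes the fix. The outcome list already includes ADC and FA, and the t-test or Mann-Whitney provision covers a continuous comparison.

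Fourth, the bottom-quarter size criteria already inflate the composite, so diffusion adds less to its false-positive rate than its stand-alone figure. That is fair, and the added effect has not been quantified. Pilot status lessens the consequence, but the results are meant to inform a larger trial, and a chance-driven case rate would carry forward.

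**Conclusion.** The point holds as a gap in a primary-outcome definition plus an inconsistent direction. If any one of 88 values suffices, about 45% to 98% of healthy infants meet the text wording and about 23% to 87% meet Table 2's, for a common correlation of 0 to 0.7. At 0.9, across both wordings and both correlation structures, the rate is about 10% to 32%. A single value would flag 4.6% or 2.3%. These figures assume normality, a well-estimated norm, RA standing for FA, and correlations that the documents do not give.

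The direction problem needs none of those assumptions. It follows from setting the criterion and Table 2 beside the Figure 4 caption.

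A reader might also infer a fixed power loss. That is not supported. Under the stated assumptions the any-region ADC rule has 46% to 75% power if one-sided and about 10% if two-sided. The advantage of a summary comes from analysing it continuously, and only if the benefit is spread over the regions averaged.

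**What to change.** In the brain-injury definition and in Table 2:

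1. Before unblinding, define one diffusion summary per infant and per measure. It can be a small set of pre-named regions, such as those reported in the pilot, or the mean z-score over readable regions with a rule for how many must be readable. Pre-named regions suit a focal effect; the mean suits a diffuse one.
2. State the direction that counts as injury separately for ADC and for anisotropy. Reconcile the text with Table 2, and RA with FA.
3. Set the 2 SD limit on the distribution of that summary in normal term infants, not on single regions.
4. Compare the summary between arms as a continuous outcome and let that comparison carry the diffusion inference. Report single-region results descriptively.

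The cost is wording and a derivation step on data already planned, with no extra scans; the summary must also be derived in the normal term infants used as the norm. There are two downsides. A focal abnormality outside the summary no longer makes a case through diffusion alone, although the qualitative white- and gray-matter scoring still captures lesions rated moderate to severe. The binary cut on a mean-z summary has low power by itself, about 21% to 45% under the uniform 0.5 SD ADC benefit with 40 per arm.

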**Study plan:**

Dating will be by ultrasound or reliable clinical dating by ACOG standards (33). A dedicated study coordinator will evaluate volunteers to enroll from pregnant patients at the Washington University Medical Center (WUMC) in St. Louis, MO. The Institutional Review Boards of WUMC will approve this study before initiation. A total of eighty consenting women will be randomized to one of two arms POM juice vs POM juice placebo in a 1:1 ratio. The Women’s Health Center at WUMC includes a State-approved collaborative practice of Washington University attending physicians, nurse practitioners, and residents that serve all patients regardless of payer status. The WUMC Center for Advanced Medicine offers a second site for recruitment where university affiliated private practices are located. We anticipate 1-2 patients enrolled per week.

***Treatment group****:* Expecting mothers in this group will be randomized to start a daily regimen of 8 oz glass of pomegranate juice (POM Wonderful). They will keep a daily diary documenting their compliance. They will continue this daily intake up until delivery of their infant.

***Placebo group:***These women will start a daily regimen of an 8 oz of pomegranate free juice placebo that matches taste, calories, and appearance to regular pomegranate juice but lacks polyphenols that contains the same substances without polyphenols. They will also keep a diary of daily intake to help ensure compliance similar to the treatment group. They too will continue to take the placebos up until the time they deliver.

***Both groups:*** All women will be followed up (called) on a weekly basis to assess compliance. Upon delivery, cord blood will be collected and sent for ellagic acid, a polyphenic component. All placental material will be sent for formal pathological exam in addition to the specialized studies outlined below.

Placental Evaluation:

**Overview**: We will test the hypothesis that the active agents in pomegranate extract modulate the villous structure of the placenta, reduces the effects of exogenous stimuli, or both, in the human placenta of women diagnosed to have intrauterine growth restriction.

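### The developmental primary cuts the Bayley score at 70 and the named tests are unadjusted; with at most 40 infants per arm, comparing the score itself would detect a general shift far more often

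*Protocol*

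**What the plan says.** Under General methods in the Biostatistical Analyses section, the protocol states: "The primary outcomes will be either a) brain injury or b) delayed development at 18-24 months". Delayed development is then defined by a single cut: "BSID III (MDI or PDI) > 2 SD (< 70) below the normal population". The Outcome measures list gives the cut slightly differently, as "> 2SD from the norm, score ≤ 70".

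The same section names the tests. For continuous data, "Continuous variables will be compared using a student t-test when they are parametric", with Mann-Whitney otherwise. Categorical variables get a chi-squared or a Kruskal-Wallis test. Covariate adjustment is not mentioned.

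On size, the Study plan says: "A total of eighty consenting women will be randomized to one of two arms", in a 1:1 ratio. No power, alpha, effect size or control rate is given, and the trial is described as a pilot for a larger one.

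Two further facts bear on the remedy. Table 1 schedules the BSID-III Cognitive, Motor and Language scales at 18-24 months, so the scores exist before they are cut. Entry requires "estimated birth weight ≤ 10th percentile for gestational age and gender" and a minimum time to the due date, so gestation and estimated fetal weight must be known before randomization.

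**The concern.** A score that runs over a wide range is reduced to yes/no at a point in its lower tail. Infants who move from 75 to 90, or from 50 to 65, then count as unchanged. With 40 per arm at most, only infants near the cut carry information about treatment, and a useful general improvement in development could easily be reported as no difference.

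The named tests also ignore entry information that is already in hand. This is the smaller part of the problem. There is no baseline Bayley score, and how well gestation and weight percentile predict the outcome is unknown.

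The protocol itself fixes both the cut and its status as a primary outcome, so the point does not depend on what a separate analysis plan may add.

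**Working it through.** The protocol has no power figure to reproduce, so the check compares the two analyses under stated assumptions.

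**Inputs from the protocol.** 80 women, 1:1, so 40 per arm at most; cut at 70; chi-squared for a categorical outcome; t-test for a continuous one.

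**Assumptions.** Two-sided alpha 0.05. SD 15, which follows if 70 is 2 SD below a norm mean of 100. Scores normal, control mean 80-90, every treated infant shifted by the same amount.

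**Event rates.** p = Φ((70 − mean)/15). For a control mean of 90, Φ(−1.333) = 9.1%; with a 7.5-point benefit, Φ(−1.833) = 3.3%. The other rates follow in the same way.

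**Power, 40 per arm.** Chi-squared (uncorrected) is by exact binomial enumeration. For the t-test, SE = 15 × √(2/40) = 3.354, so the noncentrality is 7.5/3.354 = 2.24 or 10/3.354 = 2.98.

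| Control mean | Benefit | Rates below 70 | Chi-squared | t-test on score |
|---|---|---|---|---|
| 90 | 7.5 | 9.1% vs 3.3% | 19% | 60% |
| 85 | 7.5 | 15.9% vs 6.7% | 27% | 60% |
| 80 | 7.5 | 25.2% vs 12.2% | 33% | 60% |
| 90 | 10 | 9.1% vs 2.3% | 26% | 84% |
| 85 | 10 | 15.9% vs 4.8% | 41% | 84% |
| 80 | 10 | 25.2% vs 9.1% | 50% | 84% |

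**Either score below 70.** The endpoint is MDI or PDI, so events are more frequent than with one score. With an assumed correlation of 0.6, control means of 90, 85 and 80 give control rates of 14.8%, 24.5% and 36.9%. Chi-squared power is 29%, 36% and 42% for 7.5 points. The highest value in any case tried is 63%, for 10 points at a control rate of 36.9%. If both scores are analyzed as continuous and alpha is halved, each has 50% power at 7.5 points and 77% at 10.

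**Fewer infants.** In the earlier trial 30 of 41 infants (73%) had an MRI. If Bayley follow-up left 30 per arm (assumed), the 7.5-point comparison with one score becomes 13-25% by chi-squared against 48% by t-test.

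**Adjustment.** Residual SD = 15 × √(1 − R²). With R² of 0.1-0.3 (assumed) and 3 covariate degrees of freedom, this is 14.2 to 12.5. At 40 per arm, power for 7.5 points is 64-75% against 60% unadjusted, a gain of about 5-15 percentage points. For 10 points it is 87-94% against 84%.

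**A tail effect instead of a shift.** Suppose 20-35% of controls belong to an injured group with mean 60 and SD 8, the rest have mean 95 and SD 12, and treatment halves the injured share (all assumed). With 40 per arm, chi-squared on the cut has 20-36% power and the t-test 15-30%. The ranking reverses, by about 5 percentage points.

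**The case against.** The strongest objection is that cut versus mean is a choice of what to estimate. A neuroprotectant may spare a minority from severe injury and leave the rest unchanged, and a 2-SD delay is easier to interpret clinically than a mean difference. This stands. The tail-effect calculation shows the cut slightly ahead, so the advantage of the mean depends on a fairly general shift. But the loss from choosing the mean wrongly is about 5 percentage points, while the loss from choosing the cut wrongly is about 27-58 points in the table.

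A second objection is that adjustment can be left to an analysis plan and that most of the gain is not due to it. This also largely stands: the 60% and 84% are plain t-test figures. Adjustment is an addition, not the main remedy.

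Four stronger readings are tempting and not supported:
- **The endpoint has almost no power.** That needs a low control rate, and none is stated for growth-restricted infants. With one score cut, power at 7.5 points is 1-19% for control rates up to about 9%, but the either-score definition and higher rates give more.
- **Power is lower still by Fisher's exact test.** The protocol names chi-squared, not Fisher.
- **The pilot would yield no mean or SD for planning.** The scores are collected and a t-test is named for continuous variables, so both could be reported. The protocol simply does not make them the primary result.
- **Gestation at entry will vary widely, so adjustment must gain much.** The background places diagnosis usually at the end of the second trimester, and entry closes 6 weeks before the due date. No spread is given.

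**Conclusion.** The point holds as a recommendation. For a broad improvement in development, the fixed cut at 70 gives chi-squared power of about 19-33% (7.5 points) or 26-50% (10 points), where the uncut score gives 60% or 84%. These figures rest on SD 15, a control mean of 80-90, one score, a uniform shift and full follow-up of 40 per arm, none of which the protocol states. Power on the cut stays below 80% in every shift case tried, and the continuous score does better in each of them. The ordering can reverse slightly under a pure tail effect.

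The remedy does not make the trial well powered for a half-SD effect: 64-75% with adjustment. At 5 points the unadjusted t-test has only 31%. The pilot label softens the consequence, but the protocol still names this as a primary outcome.

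**What to change.** 1. Make the primary developmental analysis a comparison of the continuous Bayley composite score, reported as a mean difference with a 95% CI.
2. Name which composite is primary. Reconcile MDI/PDI with the Cognitive, Motor and Language scales of Table 1, and the strict cut under General methods with the inclusive one under Outcome measures.
3. Adjust by ANCOVA for gestation at enrolment and estimated fetal weight percentile only. Do not adjust for birth weight, placental weight or gestation at delivery, which treatment could affect.
4. Keep the delay rate as a key secondary outcome.
5. Give deaths the worst rank in a rank-based sensitivity analysis.

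No new data are needed, but the change does alter the primary estimand. The headline becomes a mean difference, which is less directly clinical than a delay rate and less sensitive to a pure tail effect.
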